### Ethical considerations

The study will be conducted in accordance with the Helsinki Declaration 1964, including subsequent revisions. Participants will only be included after signing an informed consent based on oral and written information. The participants may, at any time, choose to withdraw from the study without being required to explain and without affecting the person's future treatment. The study is approved by the Ethical Committee of the Capital Region of Denmark (approval number H-21039423), and the project is reported to the Danish Data Protection Agency. The study investigators are under the impression that the questionnaires and investigations will not lead to any discomfort for the subjects. There are no known expected short- or long-term risks associated with the present study.

### Outcome

We hypothesize that the ZAQ will provide acceptable discrimination between ASD and SD, as indicated by an AUC ≥ 0.7. The ZAQ will retain a clinically meaningful factor structure, instructing further research on distinct sub-constructs. Lastly, the positive predictive value of the cut-off score will have strong clinical power regarding the selection of which patients need further diagnostic examination in either a specialised clinic for the assessment of psychotic disorders or a clinic for the assessment of ASD.

## Discussion

The main incentive to conduct this study has arisen from a clinical need to improve case identification of patients before referring to either ASD or SD assessment. Wrong initial case identification can lead to unacceptable clinical trajectories for the patients. An overlooked prodromal SSD in an autism clinic can delay onset of necessary treatment. A misdiagnosis of a patient in a unit for assessment of SSD can lead to treatment with antipsychotics when not warranted. Thus, incorrect referral can have severe negative consequences for the patient and is cost inefficient. ZAQ is designed to help avoid these unsatisfying trajectories and is primarily developed to alleviate difficulties in the initial case identifying phase of clinical assessment.

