### Recruitment and testing

We have designed a multicenter, prospective, non-randomized experimental study, where adult patients will be recruited from May 2022 – April 2023. A group of 300 patients will be recruited from 2 outpatient clinics located at Mental Health Centre Copenhagen: 200 patients (see power calculation) will be recruited from the pool referred to the specialised clinic for diagnostic assessment of ASD at Mental Health Centre Copenhagen, and 100 patients will be recruited from the specialised psychosis clinic at Mental Health Centre with an SD diagnosis. Additionally, a group of 200 adults from the general population without a psychiatric diagnosis will be recruited as a control group. Inclusion and exclusion criteria are detailed in Table 3. The data will be collected on-line and managed through a secure server with full compliance with Personal Data Handling laws of Denmark.

**Table 3 Tab3:** Inclusion and exclusion criteria

**Inclusion Criteria: Patients 18–65 years (ASD and non-ASD psychiatric)**	**Exclusion Criteria: Patients (ASD and non-ASD psychiatric)**
WAIS-IV or Raven IQ > 85, no-clinical suspicion of intellectual disability and minimum 11 years of education	Insufficient Danish language skills
Completion of: - Clinical Assessment - Adult Asperger Assessment (AAA) - Psychopathology evaluation using DSM-5 - A conclusion based on multidisciplinary consensus	Acute psychiatric illness prompting departure/dismissal from the diagnostic assessment
Controls: Are matched with age, gender, marital status, number of children, and educational level	Controls: Concurrent or prior psychiatric diagnosis (self-report)

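### Phase 1 cannot support the expectation that the cut-off's positive predictive value will guide referral, because every patient is sampled after referral and recruitment fixes the ASD/SD mix

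*Protocol article*

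**What the plan says.** **Intended use.** The Discussion gives the motive as the need to "improve case identification of patients before referring to either ASD or SD assessment" and says the tool is "primarily developed to alleviate difficulties in the initial case identifying phase of clinical assessment". The end of the Background, under Schizotypal disorder, also places the ZAQ at the case identification stage. The Outcome section expects that "the positive predictive value of the cut-off score will have strong clinical power regarding the selection of which patients need further diagnostic examination" at one type of clinic or the other.

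**People studied in Phase 1.** Under Recruitment and testing, 200 patients "will be recruited from the pool referred to the specialised clinic for diagnostic assessment of ASD at Mental Health Centre Copenhagen". The SD arm has a separate source, which the same paragraph gives as follows: "100 patients will be recruited from the specialised psychosis clinic at Mental Health Centre with an SD diagnosis". A further 200 controls come from the general population; Table 3 excludes those reporting a current or earlier psychiatric diagnosis. For patients, Table 3 also requires a tested IQ above 85, "no-clinical suspicion of intellectual disability and minimum 11 years of education", and an assessment that has been carried through to a multidisciplinary conclusion.

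**Phase 2.** The final questionnaire is to be validated in an independent sample. The article does not say where that sample comes from.

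**The concern.** The Outcome section makes a statement about a decision taken before referral. All Phase 1 patients are seen after that decision, and the 100 SD patients after diagnosis as well. The controls do not fill the gap, since people with no psychiatric history are not those over whom a referring clinician hesitates.

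The statement is also framed in terms of PPV, the accuracy measure most directly tied to case mix. Adding 100 diagnosed SD patients by design sets the proportion of SD in the sample, so a PPV read from the sample partly reflects the recruitment quotas. If it were reported as it stands, a referring clinician could take it as the probability that a patient flagged as SD has SD, when in their own setting that probability may be much lower.

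**Working it through.** **The plan's own figures.** The sample adds up: 200 + 100 + 200 = 500. The article gives no PPV and no pre-referral case mix, so there is no stated PPV to reproduce. The stated accuracy target is AUC ≥ 0.7 for ASD versus SD (Outcome). Sensitivity and specificity are to be read where they are equal (Concurrent validity and screening accuracy).

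**Case mix in the ASD clinic, from the audit in the Background.** Of 319 referred adults, about 37% did not meet ASD criteria, and almost 40% of those were on the schizophrenia spectrum, mostly SD. Schizophrenia-spectrum is treated here as SD.

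- ASD: 319 × 0.63 ≈ 201
- SD: 319 × 0.37 × 0.40 ≈ 47
- Neither: 319 × 0.37 × 0.60 ≈ 71

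**The same split applied to the 200 referred patients.** 126 ASD, 29.6 SD and 44.4 neither.

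- SD share of ASD + SD in the ASD clinic: 29.6 / (126 + 29.6) = 0.190
- SD share after adding the 100 SD patients: 129.6 / (126 + 129.6) = 0.507
- If all 200 are instead counted as ASD, as the abstract does: 100 / 300 = 0.333

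**Accuracy at the target.** Under an equal-variance binormal score, the point where sensitivity equals specificity is Φ(z(AUC)/√2). For AUC 0.70 this is 0.645.

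**PPV for SD.** With p the SD share among ASD + SD, PPV = se·p / [se·p + (1 − sp)(1 − p)].

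- Study mix: 0.645 × 0.507 / (0.645 × 0.507 + 0.355 × 0.493) = 0.327 / 0.502 = 0.65
- ASD-clinic mix: 0.645 × 0.190 / (0.645 × 0.190 + 0.355 × 0.810) = 0.123 / 0.410 = 0.30

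| SD share of ASD + SD | Source | PPV for SD at AUC 0.70 |
|---|---|---|
| 51% | Phase 1, audit split plus 100 SD | 0.65 |
| 33% | Phase 1, all 200 counted as ASD | 0.48 |
| 19% | ASD clinic, audit | 0.30 |
| 10% | assumed | 0.17 |
| 5% | assumed | 0.09 |

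The last two rows are assumptions, because the documents give no pre-referral mix. The 19% is itself a share after referral.

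**Sensitivity to the AUC.** Between the 51% and 19% mixes, PPV for SD falls from 0.73 to 0.38 at AUC 0.80 and from 0.82 to 0.51 at AUC 0.90. A better instrument narrows the gap only slightly. The predictive value for ASD moves the other way, from 0.64 to 0.89 at AUC 0.70.

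**What is not computed.** These figures hold sensitivity and specificity fixed and vary only the mix. They leave out the neither group and the controls. Sensitivity, specificity and AUC may also shift because Phase 1 patients are referred or diagnosed, meet IQ and education thresholds, and have a completed assessment. The documents give nothing from which to size that shift.

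**The case against.** The best defence is that the sample suits the main question. The abstract sets out to study discrimination, diagnostic accuracy and validity, and the leading hypothesis is AUC ≥ 0.7 for ASD versus SD. Phase 1 is where items are selected, and a clinic-based sample is an ordinary choice for that. The ASD-clinic patients are a referred pool, not a diagnosed one. By the audit, about 15% of such referrals (0.37 × 0.40) are on the schizophrenia spectrum, so the arm can include the misdirected referrals that motivate the tool. They complete the ZAQ alongside the clinical work-up and separately from it (Fig. 3 legend). The referral sentence is a hypothesis, and the Discussion text is motivation. All of this stands. It protects the AUC aim, but not a PPV offered as a guide to referral.

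A reader might go further in three ways that the documents do not support.

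- **That nobody in the whole study will be assessed at the intended point of use.** This is established for Phase 1 only. The article does not describe the Phase 2 setting. A condensed article may leave that out, and a suitable Phase 2 sample could close the gap.
- **That the distortion can be sized by comparison with the general population.** One could set the 63% ASD rate in the clinic against the 1.65% population prevalence, or note the share of all adults with an IQ of 85 or below. Neither comparator is the group considered for referral, and neither measures an effect on sensitivity, specificity or AUC.
- **That Phase 2 must recruit consecutive referrals as the clinics receive them.** Those people have still been referred, and to a chosen clinic. Patients who do not finish the assessment would lack a reference diagnosis, which risks partial verification. That is a debatable trade-off, not a plain correction.

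**Conclusion.** The point holds for the referral and PPV statement in the Outcome section. Phase 1 contains no patient at the pre-referral decision, and its ASD/SD mix is set by recruitment. At AUC 0.70, PPV for SD is about 0.65 at the study mix and about 0.30 at the ASD-clinic mix, so the sample value would be roughly twice the clinic value.

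These figures rest on three assumptions: the audit split applies to the 200 referred patients, schizophrenia-spectrum counts as SD, and the score is equal-variance binormal. They illustrate how strongly PPV depends on the mix and do not estimate the pre-referral PPV. Any additional spectrum effect on accuracy has unknown size.

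The hypothesis on ASD-versus-SD discrimination remains testable within specialised care, and the undescribed Phase 2 setting is not itself an error.

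**What to change.** Reword the Outcome section as follows.

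1. State the Phase 1 conclusion as ASD-versus-SD discrimination (AUC, sensitivity, specificity) among adults in specialised care who meet Table 3.
2. Make no claim from Phase 1 about selecting patients for referral.
3. Report any PPV as a table or curve over stated, assumed case mixes, calculated from the estimated sensitivity and specificity, and not from the sample proportions. Say that this handles the case mix but not a change in patient spectrum.
4. Make a referral claim only if the validation sample is drawn at or before the referral decision.

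Items 1 to 3 need rewording and a short calculation; they add no participants or assessments. The cost is a narrower stated conclusion. Item 4 is a condition on what may later be claimed and does not require a redesign of Phase 2.

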## Data Availability

The datasets used and/or analyzed during the current study are available from the corresponding author on reasonable request.

## Abbreviations

ZAQ: SchiZotypi Autism Questionnaire
ASD: Autism Spectrum Disorder
SD: Schizotypal Disorder
ADHD: Attention Deficit Hyperactivity Disorder
ADD: Attention Deficit Disorder
SSD: Schizophrenia Spectrum Disorder
RAADS-R: Ritvo Adult Asperger Diagnostic Scale Revised
SRS: Social Responsiveness Scale
SPQ-BR: Schizotypal Personality Questionnaire Brief Revised
O-LIFE: Oxford-Liverpool Inventory of Feelings and Experiences
MMS: Multidimensional Schizotypy Scale
CAPS: Cardiff Anomalous Perception Scale
CAPE: Community Assessment of Psychic Experience
MASK: Melbourne Assessment of Schizotypy in Kids (MASK)
SPQ-C: Schizotypy Personality Questionnaire in Children
Tom: Theory of Mind
CFA: Confirmatory Factor Analysis
IRT: Item Response Theory
DIF: Differential Item Functioning
RUC: Receiver Operating Characteristics
AUC: Area under the Curve
